# 1.0 Introduction

**Anxiety**

All humans experience fear and anxiety. Fear is an emotional, physiologic, and behavioral response to a recognized external threat (eg, an intruder, a runaway car). Anxiety is an unpleasant emotional state; but its causes are less clear. Anxiety is often accompanied by physiologic changes and behaviors similar to those caused by fear. [1]

Adaptive anxiety helps people prepare, practice, and rehearse so that their functioning is improved and helps them be appropriately cautious in potentially dangerous situations. Maladaptive anxiety causes distress and dysfunction. [1]

The causes of anxiety disorders are not fully known, but both physiologic and psychologic factors are involved. Physiologically, all thoughts and feelings may be understood as resulting from electrochemical processes in the brain, but this fact tells little about the complex interactions among the > 200 neurotransmitters and neuromodulators of the brain and about normal vs. abnormal arousal and anxiety. Psychologically, anxiety is viewed as a response to environmental stressors, such as the rupture of a significant relationship or exposure to a life-threatening disaster.[1]

Anxiety disorders are among the most prevalent psychiatric disorders in the Canada Post workers general population. Anxiety disorders are associated with considerable chronicity, morbidity, and disability [2,3]. Anxiety disorders impose high individual and social burden, tend to be chronic, and can be as disabling as somatic disorders. Compared with those who have other psychiatric disorders, people with anxiety disorders are high care utilizers who present to general practitioners more frequently than to psychiatric professionals, placing a strain upon the health care system and the Corporation drug benefit plan. The economic costs of anxiety disorders include psychiatric, and nonpsychiatric emergency care; hospitalization; prescription drugs; reduced productivity; absenteeism from work; and suicide [4].

Several studies have demonstrated the economic repercussions of widespread anxiety in the workplace. A data set from a large employer database has demonstrated both the medical and productivity costs of anxiety disorder. In the study, medical, pharmaceutical, absenteeism, short-term disability, and worker compensation records were collected during the year 2000 from 6 major employers. Employees diagnosed with anxiety disorders were significantly more likely to have additional diagnoses, use more services, require hospitalization, or visit the emergency room compared with the control group. In the final analysis, after controlling for differences in comorbidities, employees diagnosed with anxiety disorders had significantly higher medical costs, productivity costs, and total costs compared with the control group [5].

**Signs and Symptoms**

Anxiety can arise suddenly, as in panic, or gradually over many minutes, hours, or even days. Anxiety may last from a few seconds to years; longer duration is often associated with anxiety disorders. Anxiety ranges in intensity from barely noticeable qualms to complete panic, its most extreme form. One person's passion may be another's anxiety (eg, some find speaking before a group exhilarating, whereas others dread it), and the ability to tolerate anxiety varies from person to person [1,6].

Anxiety disorders can be so distressing and disruptive that depression may result. Alternatively, an anxiety disorder and depression may coexist, or depression may develop first, with symptoms and signs of an anxiety disorder developing later. [1,6]

Deciding when anxiety is so severe that it is a disorder depends on several variables. If anxiety is very distressing, interferes with functioning, and does not stop spontaneously within a few days, an anxiety disorder is present and merits treatment. [1,6]

Diagnosis of a specific anxiety disorder is based largely on its characteristic symptoms and signs. A family history of anxiety disorders (except posttraumatic stress disorder) is helpful, because many patients appear to have inherited a predisposition to the same anxiety disorders their relatives have as well as a general susceptibility to other anxiety disorders. [1,6]

Anxiety disorders must be distinguished from anxiety that occurs in many other psychiatric disorders, because they respond to different specific treatments. [1,6]

In Generalized Anxiety Disorder, the anxiety and worry are so great that they are difficult to control. The severity, frequency, or duration of the worry greatly exceeds what the situation, if it should occur, warrants. The focus of the worry is not restricted as it is in other psychiatric disorders (eg, to having a panic attack, being embarrassed in public, or being contaminated). Common worries include work responsibilities, money, health, safety, car repairs, and chores. A person with this disorder must also experience three or more of the following symptoms: restlessness, unusual fatigability, difficulty concentrating, irritability, muscle tension, and disturbed sleep. The course is usually fluctuating and chronic, with worsening during stress. [1,6]

**Conventional Treatment**

Benzodiazepines (Alprazolam, Chlordiazepoxide, Clonazepam, Clonazepate, Diazepam, Lorazepam, Oxazepam) in small to moderate doses are often prescribed, although sustained use can cause physical dependence. Consequently, the benzodiazepine should be tapered slowly rather than stopped abruptly, if it is to be discontinued. The relief obtained usually outweighs any mild adverse effects and the possibility of drug dependence. [1]

Buspirone is also effective for some patients, although its onset of effect takes about 2 wk, whereas benzodiazepines work within minutes. Buspirone does not cause dependency. Some antidepressants are also effective. [1]

The benefits of behavior therapy are limited because specifying anxiety triggers to which the person can be exposed is difficult. Relaxation and biofeedback may be of some help, although few studies have documented their efficacy. Insight-oriented psychotherapy has not been systematically studied in this disorder. [1]

**Naturopathic Treatments for Anxiety**

Herbs are powerful substances from which many pharmaceutical drugs have been formulated, yet there is a sense in the public domain that herbs are ‘natural’ and therefore harmless. In comparison, conventionally prescribed pharmaceutical drugs are often seen as fraught with risk and causing multiple adverse effects [7,8]. Evidence has shown, however, that herbal medicines can be harmful and that health care professionals need more education concerning the risks of these medicines [9-12]. It should also be noted that herbal medicines have a long tradition of use and many have been shown to be effective for a wide range of conditions. While numerous studies have been performed on Withania somnifera, there are only animal studies indicating its use as an anxiolytic. In an animal study assessing the anxiolytic and antidepressive actions of Withania somnifera compared to commonly prescribed pharmaceuticals, an extract of the root was administered orally to rats once daily for five days [13]. The results were compared to a group administered the benzodiazepine lorazepam for anxiolytic activity, and the tricyclic antidepressant imipramine for antidepressant investigation. Both the ashwagandha group and the lorzepaam group demonstrated reduced brain levels of a marker of clinical anxiety. Other similar studies confirm these results, lending support to the use of ashwagandha as an antistress adaptogen. [14-17]

A study showing the role of a Withania extract on CNS calcium antagonism, sheds some light on a potential mechanism of anxiolytic action.  With Withania extract supplementation the extracellular neuronal results obtained were consistent with calcium antagonistic properties, thereby counteracting excitation.  Calcium excitation plays a role in various psychiatric conditions including anxiety [18].

Diets high in stimulants have been linked to symptoms of anxiety. Reducing stimulants such as caffeine, chocolate, nicotine, refined sugars will reduce incidence and severity of anxiety [19]. Studies have shown that reduction in fat and alcohol also reduces the vulnerability to stress responses [20, 21].

Cognitive behavioural interventions such as diaphragmatic breathing have been shown to reduce anxiety levels and improve coping capability in stressful situations [22]. Therapies identifying negative stress coping patterns and replacing them with positive outlets are effective means of controlling and treating anxiety [23].

**Safety**

In addition to the criteria for measuring efficacy, there will also be assessment for harm and adverse effects that might arise from ingesting Whithania somnifera, or the Adult Multi One multivitamin. Participants will be monitored periodically by a naturopathic doctor and adverse events will be documented. If the participants feel as if their health is compromised in any way or the qualified investigator feels as if their health is compromised, they will immediately discontinue the trial and if necessary be referred to their medical doctor for further care. In addition, if any significant health issues arise independent to the trial, the participants will also discontinue the trial and be referred to their medical doctor. If it is found that the health of any of the participants is compromised in any way, they will be immediately pulled from the study. Approval has been sought and granted from the ethics review board of the Canadian College of Naturopathic Medicine. Approval is also being requested from Health Canada and is necessary before beginning the study. It should be noted that Withania somifera, and the Adult Multi One multivitamin are already on the market and any determination of harm is crucial for public safety and should be disseminated rapidly and effectively. If on the other hand, any efficacy is found then the public will also be so informed giving an alternative option for treatment of anxiety perhaps without increased risk of complications or sedation.

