On subsequent visits, both the control and intervention group patients will receive treatments including cognitive behavioural stress reduction, behavioral psychotherapy, examination of sleep patterns and treatment for any insomnia. Both groups will be encouraged to engage in an active exercise routine. The active group will also receive daily good quality multi vitamin (Ultra Balance III by Douglas Labs) and *Withania somnifera* (300 mg standardized to 1.5% Withanolides, bid) (Ashwagandha by Douglas Labs). The control group will receive placebo identical in look and frequency of dosage to the treatment group. On subsequent visits, the active group will receive lifestyle and diet counseling, and will continue with behavioral psychotherapy. Active group patients will also receive acupressure massage for at least 15 minutes once per week.

Both the active and control arm will attend weekly 30 minute treatments, for a total of 12 treatments over 12 weeks. Both groups will complete the Beck Anxiety Inventory, S-90-R, SF-36, Fatigue Questionnaire, and the Perceived Benefit of Treatment questionnaires at 4, 8, and 12 weeks. At these times, the sitting and orthostatic blood pressures will also be recorded. Both groups will also hand in the Pain Diet, Absenteeism, Pain Medication and Therapies Diary every week.

Study period is 12 weeks. Clinical evaluations will be performed at:

- Baseline (Visit 1 - Day 1)
- Interim for the treatment groups: (Visit 2 - Day 7, Visit 3- Day 14, Visit 4 – Day 21, Visit 4 – Day 28, Visit 5 – Day 35, Visit 6 – Day 42, Visit 7 – Day 49, Visit 8 – Day 56, Visit 9 – Day 63, Visit 10 – Day 70, Visit 11 – Day 77)
- Interim for the control groups: (Visit 2 - Day 7, Visit 3- Day 14, Visit 4 – Day 21, Visit 4 – Day 28, Visit 5 – Day 35, Visit 6 – Day 42, Visit 7 – Day 49, Visit 8 – Day 56, Visit 9 – Day 63, Visit 10 – Day 70, Visit 11 – Day 77)
- End of Treatment (Visit 12 - Day 84), Questionnaires and Medication diaries filled in for the last time

Follow-up data will be collected at 2, 6, and 12 months post treatment via a mailed questionnaire package containing the Beck Anxiety Inventory, S-90-R, SF-36, Fatigue Questionnaire, and the Perceived Benefit of Treatment questionnaires, as well as the Diet, Absenteeism, Medication and Therapies Diary. Non-responders will receive reminders by post. If this is unsuccessful, the patients will be telephoned.

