**Sample size determination**

Assuming a normal distribution with variances between both populations (pre and post treatment) being essentially equal, we made our power size calculations using Jan deLeeuw's Web-Based Statistics: The Study of Stability in Variation[24]. To obtain a power of 80% with a two sided 5% significance level we would need 54 participants to complete this two-treatment parallel-design study. This will enable the detection of a 40% difference in the Beck Anxiety Inventory rating scale, an amount considered to be clinically significant. Assuming a drop out rate of 30% we will need 78 subjects to commence the trial so that 54 will complete the trial.

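### The Safety section treats stopping for a health reason as leaving the study, so later BAI scores go uncollected, and the Day 84 comparison can be biased if such removals differ between arms

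*Protocol*

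**What the plan says.** The Safety part of section 1.0 gives three triggers, and each ends participation.

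- If the participant or the qualified investigator feels that health is compromised, "they will immediately discontinue the trial and if necessary be referred to their medical doctor for further care".
- For problems unrelated to the trial, "if any significant health issues arise independent to the trial, the participants will also discontinue the trial".
- If health is found to be compromised in any way, "they will be immediately pulled from the study".

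The scientific abstract and the Schedule of events place the BAI at Days 28, 56 and 84. Neither says what happens to these assessments after a removal. The Withdrawal from Study form records the date, any link to an adverse event and the reason, but no outcome score and no follow-up status.

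The only retention measure is in Methodology: "Non-responders will receive reminders by post. If this is unsuccessful, the patients will be telephoned". It belongs to the questionnaires mailed 2, 6 and 12 months after treatment, and withdrawn participants are not mentioned.

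The Sample size determination section says: "To obtain a power of 80% with a two sided 5% significance level we would need 54 participants to complete this two-treatment parallel-design study". It then allows for loss: "Assuming a drop out rate of 30% we will need 78 subjects to commence the trial so that 54 will complete the trial".

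**The concern.** The protocol has no state in which a participant is off treatment but still assessed. Read literally, the rule stops BAI collection in people who are doing badly.

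The triggers can overlap with the endpoint. The BAI in Appendix A counts dizziness, a pounding heart, difficulty in breathing and indigestion. Someone with these symptoms may feel unwell enough to be removed, and a high score is then lost.

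Removals could also differ by arm. According to Methodology, only the active arm receives Withania, the multivitamin and weekly acupressure. The design is described as single blinded, and a trigger can be the participant's or investigator's own impression.

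At stake is whether the people with a Day 84 BAI still represent the groups that were randomised. A statistical analysis plan can choose an analysis set and a missing-data method, but it cannot supply scores that the protocol stopped collecting. The point therefore belongs in the protocol.

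**Working it through.** **1. The plan's own figure.** Inputs from Sample size determination: 54 completers and 30% dropout. 54 / (1 − 0.30) = 77.1, rounded up to 78, as stated. The planned loss is 78 − 54 = 24, and 24/78 = 31%. This is dropout from every cause. The document gives no rate for health removals.

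**2. The effect that 54 completers can detect.** The protocol states "This will enable the detection of a 40% difference in the Beck Anxiety Inventory rating scale" but gives no SD or control mean, so the 54 cannot be derived from its inputs. Working backwards with 27 per arm (1:1 allocation assumed), two-sided 5%, 80% power and a noncentral t distribution, the standardised difference is 0.777.

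**3. Bias formula.** Let m be the fraction of an arm with no Day 84 BAI, and g the amount, in SD, by which the missing participants score worse than those observed. The observed mean of that arm is then off by m × g. The bias in the arm difference is m₁g₁ − m₂g₂. All values of g are assumptions.

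**4. Same loss for the same reasons.** With m = 0.30 and the same g in both arms, the bias is 0.30g − 0.30g = 0. Type I error stays at 5%, and only power is lost.

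**5. Loss of 30% per arm, outcome-related in one arm and random in the other.** The bias is 0.30 × g. Type I error is from the noncentral t with 27 per arm.

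| g (SD) | Bias (SD) | Share of 0.777 | Type I error |
|---|---|---|---|
| 0.25 | 0.075 | 10% | 5.8% |
| 0.5 | 0.15 | 19% | 8.4% |
| 1.0 | 0.30 | 39% | 19.1% |

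**6. Only a quarter of the dropout is health removal (assumed), same one-sided pattern.** The bias is 0.25 × 0.30 × g = 0.075g. For g = 0.5 it is 0.0375 SD, with error 5.2%. For g = 1.0 it is 0.075 SD, with error 5.8%.

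**7. Unequal loss, same gap in both arms (39 randomised per arm, normal approximation).** The bias is the difference in loss rates × g.

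- 35% against 25%, g = 0.5: 0.10 × 0.5 = 0.05 SD, error 5.4%.
- 40% against 20%, g = 1.0: 0.20 × 1.0 = 0.20 SD, error 11.3%.

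More extreme assumptions give more: 50% against 10% with g = 1.0 gives 0.40 SD and 29%. The 0.30 SD in step 5 is thus the top of the range used here and not a mathematical bound.

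**8. Cost of including off-treatment scores.** Suppose 30% of participants stop treatment and keep none, or half, of an effect of 0.777 SD.

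- None kept: 0.777 × 0.70 = 0.54 SD. Power is 50% with 54 analysed and 66% with 78.
- Half kept: 0.777 × 0.85 = 0.66 SD. Power is 66% with 54 analysed and 82% with 78.

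**The case against.** The strongest reply is that little of this loss is documented. The Safety text is introductory and never mentions questionnaires. One rule covers both arms, and equal loss for the same reasons causes no bias. Many removed participants would already have a Day 28 or Day 56 BAI that an analysis could use, and the mailed follow-up is not expressly limited to completers. All of this stands and limits the size of the problem. It does not restore the Day 84 score, and mailings that begin two months after treatment do not replace it.

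A reader might go further and infer three things that the document does not support.

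- **That up to 30% of participants will be lost for outcome-related reasons.** The 30% is all-cause dropout, and nothing ties it to the Safety rule. Shift conflicts or loss of interest would count towards it too.
- **That the protocol specifies a completers-only analysis.** Dividing by 1 − 0.30 is routine and correct, and does not define an analysis set. Statistical Analysis names tests but no population. The analysis set and the handling of missing data may stand in an analysis plan that is not shown.
- **That the null hypothesis cannot be tested without bias.** Bias needs loss that differs between arms in rate or reason. That is possible here but not established.

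**Conclusion.** The point holds in a limited form. The Safety section equates stopping for a health reason, even one unrelated to the trial, with leaving the study. No text shown provides for the BAI at Days 28, 56 and 84 afterwards. The Day 84 comparison can therefore be biased if removals differ between arms in rate or reason, and later analysis cannot recover the missing scores.

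The size is unknown. The illustrated 0 to 0.30 SD, with type I error from 5% to about 19%, rests on assumed gaps between missing and observed participants. Its upper end further requires that all the planned dropout in one arm is related to outcome and all of it in the other arm is random. With a quarter of the dropout due to health removal, the error is about 5-6%. A change is still worthwhile because the remedy is cheap and the lost scores are irrecoverable.

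**What to change.** Leave the clinical decision to stop treatment exactly as it is, and change only data collection.

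- In the Safety section, state that stopping the intervention is not leaving the study. Participants who stop and still consent complete the BAI and the other questionnaires at Days 28, 56 and 84.
- Use for this the mail and telephone route that Methodology already sets up for the later follow-up.
- On the Withdrawal from Study form, add a line recording whether the participant stopped treatment only or also follow-up.

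The cost is a sentence or two of protocol text, one line on a form and a few extra mailings. The estimate will include time off treatment and so may be smaller. For that reason, 54 participants with a Day 84 BAI should not be presented as keeping 80% power for that estimate. Under the assumptions in the last step of the working, 54 gives about 50-66%.

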**Intervention:** Baseline assessment of both groups will include blood pressure, orthostatic blood pressure, and completion of the Beck Anxiety Inventory (BAI), SF-36, and The Fatigue Questionnaire to determine severity of anxiety symptoms. The active group will receive instruction on stress reduction techniques including diaphragmatic breath control, encouragement to exercise, counselling to identify and eliminate negative stress coping patterns, dietary counselling to ensure proper nutritional content of foods, and reduce reactive hypoglycaemia, Withania somnifera, and a multi vitamin for 12 weeks. The control group will receive instruction on stress reduction techniques including diaphragmatic breath control, encouragement to exercise, counselling to identify and eliminate negative stress coping patterns, and placebo. Every 4 weeks (day 28, day 56) both groups will again have their sitting and orthostatic blood pressure checked, and complete the BAI, SF-36, and The Fatigue Questionnaire. On day 84, a final assessment of sitting and orthostatic blood pressure, BAI, SF-36, and The Fatigue Questionnaire completion will take place.

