**Main Outcome Measures:** ***The Beck Anxiety Inventory (BAI)*** is designed to discriminate anxiety from depression in individuals. The BAI consists of 21 items, each describing a common symptom of anxiety. The items are summed to obtain a total score that can range from 0-63. The scale has high internal consistency. ***The short form –36*** (SF-36) questionnaire is a self-administered, 36-item questionnaire that measures health-related quality of life in eight domains: 1) physical functioning, by measuring the ability to perform a variety of daily activities and tasks that require physical effort (10 items); 2) role limitations due to physical problems(4 items); 3)role limitations due to emotional problems (3 items); 4) vitality, measuring perceived level of energy and fatigue (4 items); 5) freedom from bodily pain (2 items); 6)social functioning (2 items); 7) mental health, by measuring both negative and positive emotional states (5 items) and 8)general health perceptions (6 items). Both physical and mental summary scores can be obtained. Each domain is scored separately from 0 (lowest level) to 100 (highest level). Two summary scores can be calculated from information obtained in the 8 domains- Physical Function and Mental Health Summary Scores. ***The Fatigue Questionnaire*** is an 11-item instrument developed for use in population studies to measure physical and mental aspects of fatigue, a feature commonly observed in many somatizing patients. Each item has 4 response options, with high scores corresponding to high levels of fatigue.

**Relevance:** Many patients seek alternatives to conventional anxiety treatments. To date, no study has evaluated the potential for the combined efficacy of dietary, counselling, exercise, Withania somnifera and a Adult Multi One multivitamin to effectively treat anxiety. Knowledge of the efficacy, safety or risk of natural health products, especially one already on the market is important for physicians and the public in order to make informed decisions.

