## 3.3 Timeline

1. Labelled as day 0, all potential candidates will be screened for inclusion/exclusion criteria by being asked to read and sign the informed consent, fill in questionnaires including the BAI, be clinically assessed, have their blood pressure taken, and have urine tests to assess for proper liver and kidney function.

1. On day 1, participants that have fulfilled all eligibility criteria and completed the consent form will be randomised into either treatment or control groups using a random number generator by the research assistant who will label the containers of placebo, *Withania somnifera* and multivitamin respectively.
2. Both treatment and placebo groups shall receive the visually identical capsules by the study co-ordinator with instructions on the dosage schedule.
3. Both groups shall take their medications twice daily, one capsule in the morning and one in the evening prior to meals.
4. The treatment shall last 90 days.
5. On day 1, subjects will be clinically assessed, have their blood pressure taken, be interviewed, and complete the SCL-90R, SF-36 and fatique questionnaires. Medication usage will be monitored and compliance to the interventions will be assessed.
6. On day 7, subjects will receive cognitive–behavioral therapy, dietary advice and stress reduction techniques. They will continue these treatment sessions 1 time per week until the completion of the study. (Day 14, 21, 28, 35, 42, 49, 56, 63, 70, 77 and 84)
7. On day 8, subjects in the active group will receive acupressure massage in the treatment of anxiety. They will continue these treatment sessions 1 time per week until the completion of the study. . (Day 15, 22, 30, 38, 45, 52, 60, 68, 75, 82 and 90)
8. On day 28, subjects will be clinically assessed, have their blood pressure taken, be interviewed, and complete the SCL-90R, SF-36 and fatigue questionnaires
9. On day 56, subjects will be clinically assessed, have their blood pressure taken, be interviewed, and complete the SCL-90R, SF-36 and fatigue questionnaires
10. On day 84, subjects will be clinically assessed, have their blood pressure taken, be interviewed, and complete the SCL-90R, SF-36 and fatigue questionnaires

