**Outcome measurements**

We will determine if naturopathic medical interventions (*Withania somnifera* extract, daily multi-vitamin, dietary modifications, cognitive-behavioral exercises, relaxation techniques and acupressure massage) reduces the incidence of specific symptoms as measured by the Beck Anxiety Inventory as shown in appendix A. This scale has been independently validated.

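### The protocol describes the randomised contrast inconsistently: acupressure, and in some sections diet counselling, goes to the active arm only, so an arm difference cannot be credited to Withania and the multivitamin

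*Protocol*

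**What the plan says.** Section 2.0 (Participants) gives dietary modification, exercise and counselling to both arms and separates them only by Withania plus multivitamin versus placebo. The Intervention paragraph of the same section lists "dietary counselling to ensure proper nutritional content of foods, and reduce reactive hypoglycaemia, Withania somnifera, and a multi vitamin for 12 weeks" for the active arm and names no dietary element for the control arm. Neither paragraph mentions acupressure, and neither does section 3.0.

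Methodology adds it: "Active group patients will also receive acupressure massage for at least 15 minutes once per week". It also restricts diet counselling: "On subsequent visits, the active group will receive lifestyle and diet counseling, and will continue with behavioral psychotherapy". Section 3.3 agrees on acupressure ("On day 8, subjects in the active group will receive acupressure massage in the treatment of anxiety"), but gives dietary advice from day 7 to subjects without restriction by arm. Outcome measurements describes the intervention under study as the supplements together with "dietary modifications, cognitive-behavioral exercises, relaxation techniques and acupressure massage".

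On what the trial will tell others, the Safety text in section 1.0 says that "Withania somifera, and the Adult Multi One multivitamin are already on the market" and that any harm should be made known quickly. The next sentence reads: "If on the other hand, any efficacy is found then the public will also be so informed giving an alternative option for treatment of anxiety". The Relevance paragraph of section 2.0 adds: "Knowledge of the efficacy, safety or risk of natural health products, especially one already on the market is important for physicians and the public".

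**The concern.** A reader of the abstract alone sees a placebo-controlled test of two supplements on top of identical care. By Methodology and section 3.3 the active arm also receives a weekly hands-on treatment that section 3.3 itself describes as being for anxiety. The placebo matches the capsules but nothing matches the massage or its contact time. The main outcome is self-reported, and an active-only procedure may also reveal allocation.

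At stake is what a positive result means. Read against the abstract, it would credit the supplements with whatever the massage, and possibly the diet counselling, contributed. The objective and null hypothesis have a second gap. They name exercise and counselling among the things tested, yet both arms receive these, so the comparison says nothing about them.

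**Working it through.** **Step 1. The arm descriptions side by side.**

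| Protocol section | Acupressure | Diet counselling or advice | Active minus control |
|---|---|---|---|
| 2.0, Participants | not mentioned | both arms | products |
| 2.0, Intervention | not mentioned | active list only | products + diet |
| Methodology | active only, weekly | active only | products + acupressure + diet |
| 3.3 Timeline | active only, weekly from day 8 | subjects, no restriction | products + acupressure |

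Here, products means Withania plus multivitamin against placebo. No two rows give the same contrast. Section 3.0 names the package without acupressure; Outcome measurements names it with acupressure.

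**Step 2. What the comparison identifies.** Write P for the joint effect of the products, A for acupressure, D for diet counselling where it is active-only, and S for shared care. Ignoring interactions:

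- active arm = S + P + A (+ D)
- control arm = S
- arm difference = P + A (+ D)

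This is one observed difference with two or three unknowns. P can be any share of it, from none to all. S cancels, so shared care is not tested. The herb and the multivitamin are always given together, so even with A and D equalised only their joint effect could be estimated. Neither a larger sample nor a different analysis changes this.

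**Step 3. How much active-only contact.** Section 3.3 lists acupressure on days 8, 15, 22, 30, 38, 45, 52, 60, 68, 75, 82 and 90. Eleven of these fall before the day 84 assessment. At the 15-minute minimum in Methodology, 11 × 15 = 165 minutes. Shared sessions are 12 × 30 = 360 minutes. If acupressure is additional, as the separate days suggest, that is 165/360 = 46% more contact time. The protocol does not say outright that it is additional.

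**Step 4. The plan's own figures.** Enrolment reproduces: 54/0.7 = 77.1, rounded up to 78. The 54 completers cannot be reproduced, because Sample size determination gives no standard deviation or reference mean. Assuming 1:1 allocation (not stated), there are 27 per arm. The detectable standardised difference is then (1.96 + 0.842)/√(27/2) = 0.76, or 0.78 with the t distribution.

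**Step 5. A purely hypothetical illustration.** Suppose the products do nothing and the other active-only care shifts the BAI by d standard deviations. The chance of a significant result favouring the active arm is Φ(d√(27/2) − 1.96):

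- d = 0: 0.025
- d = 0.2: 0.11
- d = 0.3: 0.20
- d = 0.5: 0.45
- d = 0.8: 0.84

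The documents support none of these values of d. The list shows only that a significant result is not in itself evidence about the products.

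**The case against.** The tempting stronger reading is that the protocol promises the public an efficacy message about the marketed products. The documents do not go that far. The Safety sentence on efficacy names no product; the sentence before it names both, but in connection with harm. The Relevance paragraph of section 2.0 makes no promise, and the sentence before the one quoted concerns combined efficacy. The abstract's background, objective and null hypothesis, Outcome measurements, and the Relevance text in section 5.3 all address a combined or typical naturopathic approach. No stated hypothesis or analysis isolates either product. This objection stands: the product reading is natural from the wording, but it is an inference.

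It can also be said that a multi-component intervention is a legitimate choice, that inseparable components come with it, and that the package-against-control comparison remains available. That stands too. A reader might infer that the comparison is worthless, and it is not. Nor does any assumed effect of acupressure measure the actual problem, since none is given in the documents and the allocation ratio is unstated.

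The contradiction survives these points. The package in the abstract and in section 3.0 omits acupressure, so even a package-level conclusion worded from those sections would describe something other than the active arm of Methodology and section 3.3.

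**Conclusion.** The point holds as an inconsistency about what is randomised, with a consequence for attribution. Four arm descriptions imply four contrasts. Acupressure is active-only in both operational sections that assign it to an arm; the position of diet counselling is contradictory. On any version with active-only care beyond the capsules, the supplements' share of a BAI difference is not identified, and the shared components are not tested on any version. No stated number is shown to be wrong, and no randomisation, endpoint or sample size depends on the correction. The conclusion rests only on the arm descriptions; the contact-time figure assumes that acupressure is additional, and the probabilities in step 5 are hypothetical. It is worth correcting because it decides what a positive result may be said to show.

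**What to change.** 1. Reconcile the arm descriptions in section 2.0 (Participants and Intervention) and section 3.0 with Methodology, section 3.3 and Outcome measurements. If acupressure is delivered as Methodology and section 3.3 have it, name it wherever the active arm is described.
2. Settle which arm or arms receive diet counselling and state it identically throughout. The efficacy conclusion cannot be worded until this is done.
3. State in the objective, the null hypothesis, the Safety text and the Relevance paragraph of section 2.0 that the efficacy conclusion concerns only the combined active-only components over the care both arms share. Add that no efficacy claim will be made for Withania or the multivitamin alone.

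The cost is wording and a narrower conclusion. A claim about the supplements would need a different design, with all other care the same in both arms, and would still cover only the two supplements jointly.
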